### Safety, and monitoring of serious adverse events and other medical events

Data are collected at in-person visits and if contacted by a participant between visits regarding any medical issues that might affect safety of the intervention or outcomes (e.g. pregnancy). Serious adverse events are defined as hospitalizations, fatal or life-threatening events, events resulting in significant or persistent disabilities, birth defects or congenital abnormalities, or important medical events that investigators judge to represent significant hazards or harm to research subjects. Other medical events and alert values for assessments of clinical relevance are also monitored and reported to participants. Standard guidelines are used to determine alert values and recommend medical follow-up to participants for blood pressure, lipid and glucose levels. If a participant has a greater than 20% weight loss from baseline, reaches a BMI ≤ 18.5 kg/m^2^ or loses more than 15 pounds in a month, the participant is seen and counseled. If further weight loss occurs, intervention activities are suspended. If a participant develops an eating disorder, the participant is referred to care, and intervention is discontinued and not resumed until cleared by their care provider. Intervention activities are also stopped during pregnancy or if there are injuries or illnesses where weight loss and/or physical activity would be contra-indicated. Intervention is resumed 6-months post-partum or when injuries or illnesses resolve.

### Procedures for minimizing dropouts and improving retention

A systematic protocol is followed to minimize dropouts. Participants in the intervention are called or sent an email reminder before each session. If a participant has an unexpected absence, they are contacted and helped to solve any barriers to attendance. The session materials are emailed or sent to those who do not attend and a make-up session is offered. Top priority is for assessment visits. At baseline, names and addresses of several friends and family members who can be contacted are obtained for use if we lose touch with the participant. Birthday cards, holiday cards an annual token gift, and periodic newsletters are also to improve retention. The biggest source of dropouts in prior studies with this age group is pregnancy (15% of women in Health Hunters [41] had a pregnancy; 11% of the women in POP [13]). We stay in touch with women during pregnancy and allow them to return to the study at 6 months post-partum; we continue to include their weight data in our analyses except during their actual pregnancy and the 6-months post-partum.

### Sample size calculation

The targeted sample size (N=600 total; N=200/arm) is projected to provide ≥ 90% statistical power to detect an average pairwise difference of 3.0 lbs (1.36 kg) weight change over time between intervention arms, while accommodating anticipated rates of lost follow-up (an accumulating 7.5% at Month 4, an additional 7.5% at Month 12, and 5%/year thereafter). Comparisons of this primary outcome will be based on generalized linear models for longitudinal data. The targeted sample size provides 90% power to detect a relative 28% reduction in the proportion of participants who gain weight over time, an important secondary outcome, based on generalized estimating equations.

### Analysis plan

The primary outcome measure, changes in weight from baseline over time, is assessed at 4-, 12-, 24-, 36- (80% of cohort), and 48-months (20% of cohort). All measured weights will be included in the analyses, except any that may have occurred during a pregnancy or within 6 months post-partum. Weight changes will be contrasted among intervention groups using generalized linear models fitted by maximum likelihood with an unstructured covariance matrix [42], with clinic site included as a covariate. Estimated mean differences for each pairwise comparison will be developed using linear contrasts and assessed with Wald statistics, using Bonferroni adjustment to control total Type I error to be 0.05 across the three comparisons.

In the primary analysis, missing weight measurements will be assumed missing at random, but additional analyses will be conducted related to missing data (e.g. comparing baseline characteristics of completers vs non-completers and creating propensity scores). If missing data appear to have the potential of influencing interpretations, we will also conduct multiple imputations using several different models for non-ignorable missingness. These will be used to assess the range of impact that missing data may exert on our results. To gauge the sensitivity of our results to any changes in height, we will conduct supporting analyses of changes in BMI.

The secondary aims will be examined as follows. Pairwise differences in the secondary outcome measure, weight gain of greater than 1 pound from baseline (yes/no), will be assessed using generalized estimating equation (GEE) methods. Pairwise differences in mean weight changes from baseline to 24 months post-randomization among intervention arms will be assessed with linear contrasts and Wald tests within the framework of the general linear models used for the primary aim. Two-sided tests will be used with Bonferroni-adjustment to maintain overall Type I error for this secondary aim at 0.05. Generalized linear models will be used to compare the changes in behaviors and risk factors over time among the three treatments in a manner similar to that used for assessing weight changes. The effects of demographic and psychological measures on the outcomes will be examined by including initial BMI, ethnicity, age, scores on the eating inventory, and intervention preference. Significant interaction effects will be plotted to illustrate the moderating effects, further assisting the interpretation for whom and under what circumstances the intervention has different effects. To examine potential mediators of the effect of intervention, i.e., whether or not there is evidence that changes in diet, physical activity, restraint, and self-regulatory behaviors may be in the causal pathway between the intervention and weight gain, a series of three linear regression models will be fitted to test for mediators following the procedures introduced by Baron and Kenny [43]. The Sobel’s test will be used to test the significance of the indirect effect. The joint effects of multiple mediators will also be tested [44]. For the secondary outcome of weight gain (yes/no), logistic regression models will be fitted to assess meditational effects [45].

We pre-specify three planned subgroup comparisons. We will assess, using tests of interaction, whether the relative efficacy of the intervention varies according to baseline BMI (<25 kg/m^2^ versus ≥25 kg/m^2^), age (<25 years versus ≥25 years), and gender.

The fidelity of intervention delivery within the two clinical sites will be assessed by comparing measures of adherence and weight control. Adverse events will be tallied by intervention assignment and for important clinical subgroups. We will report event rates per person years and use Poisson regression to compare rates of any commonly occurring events among intervention groups.

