#### Self-regulation plus large behavior changes group

The focus of this intervention group is on making periodic large changes in diet and physical activity, with the goal of losing 5–10 pounds to buffer against the weight gain that often occurs during young adulthood. Recognizing that it is challenging for young adults to pay close attention to diet and exercise at all times, this group is encouraged to spend a few weeks each year really focusing on diet and exercise to produce a 5–10 pound weight loss, and then throughout the rest of the year, focus on weighing themselves regularly and maintaining healthy eating habits and high physical activity levels to prevent weight regain (see Table 4 for specific lesson topics).

**Diet** Individuals with a BMI of 21–24.9 kg/m^2^ are encouraged to lose 5 pounds; those with a BMI of 25–30 kg/m^2^ are encouraged to lose 10 pounds. To produce these weight losses, participants in the Large Changes group are instructed to consume either 1200–1500 or 1500–1800 calories per day, with <30% of calories from fat. The specific calorie range is individualized based on baseline weight and physical activity. To stay within their recommended calorie range, participants are taught about calorie balance and about the calorie content of different types of foods. They are given a variety of low calorie low fat eating plans that they can use since this type of structure has been shown to improve weight loss [27]. They continue to follow the reduced calorie diet until they achieve their prescribed weight loss goal, which is expected to occur for many by the end of the initial 8 week program. After reaching their weight loss goal, their calories are gradually increased to maintain this reduced weight level and a healthy, low calorie, low fat regimen is encouraged.

**Exercise** Large Changes participants are instructed to gradually increase their physical activity until achieving 250 minutes per week (5 days/week with 50 minutes per day) using activities similar in intensity to brisk walking and are encouraged to maintain this high level of activity over all subsequent years of the program.

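### The primary change-from-baseline model names clinic site as its only covariate; prespecifying baseline weight would add modest precision and remove chance-imbalance error at almost no cost

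*Protocol article*

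**What the plan says.** The protocol article, under Analysis plan, defines the response as "The primary outcome measure, changes in weight from baseline over time", measured at 4, 12, 24, 36 and 48 months. The arms are compared with "generalized linear models fitted by maximum likelihood with an unstructured covariance matrix", "with clinic site included as a covariate". Pairwise contrasts are Wald tests, "using Bonferroni adjustment to control total Type I error to be 0.05 across the three comparisons". The 24-month comparison is a contrast within the same model, and the behaviour and risk-factor outcomes are to be handled similarly.

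The Randomization section stratifies by site, gender and ethnicity. The Study design section mentions clinical center alone. Neither includes baseline weight or BMI. Table 5 shows weight measured at month 0.

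Baseline BMI appears elsewhere. It is a candidate predictor and moderator in the secondary aims, and it defines one of three prespecified interaction tests (below 25 versus 25 and above). In the Large Changes arm the weight-loss target depends on it: 5 lb below BMI 25, while "those with a BMI of 25–30 kg/m^2^ are encouraged to lose 10 pounds".

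The Sample size calculation section claims "≥ 90% statistical power to detect an average pairwise difference of 3.0 lbs (1.36 kg) weight change over time" with 200 per arm.

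**The concern.** A change score is follow-up minus baseline, so any within-person fluctuation in baseline weight enters the change with a negative sign. Heavier participants may also change differently from lighter ones, and the plan itself lists initial BMI as a possible predictor of weight change. Either would give a within-arm correlation between baseline weight and change.

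If that correlation is not zero, an analysis of change without baseline as a covariate has two costs. Its residual variance is larger than it needs to be. And if the arms happen to differ in baseline weight, which the stratification does not prevent, part of that difference carries over into this trial's treatment estimate. Both costs are avoidable with a variable that is already collected.

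**Working it through.** **Inputs from the article.** Design difference 1.36 kg; 200 per arm; total Type I error 0.05 over three comparisons, so 0.0167 each. Losses are 7.5% at month 4, a further 7.5% at month 12 and 5% per year after that. I read this as 20% at month 24, leaving 200 × 0.80 = 160 per arm.

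**Assumptions.** Two-sided testing of the primary contrasts (the article states "Two-sided tests will be used with Bonferroni-adjustment" for the 24-month aim only), a normal approximation, and r, the within-arm correlation of baseline weight with weight change. The article gives no value for r, so a range is used.

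**1. The plan's own figure.** The stated power cannot be reproduced, because the article gives neither the SD of weight change nor the within-person correlation. It can only be back-solved. The largest SD that gives 90% power is

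SD = 1.36 / [√(2/n) × (2.394 + 1.282)].

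At alpha 0.0167 this is 3.70 kg for n = 200, 3.31 kg for n = 160 and 3.20 kg for n = 150. The steps below use n = 160 and SD 3.31 kg, so the unadjusted analysis starts at exactly 90%.

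**2. Precision.** Adjustment multiplies the SD by √(1 − r²), so the variance falls by r². Power becomes Φ(3.676/√(1 − r²) − 2.394).

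| r (assumed) | Variance reduction | Power | n per arm for 90% |
|---|---|---|---|
| 0 | 0% | 90.0% | 161 |
| 0.1 | 1% | 90.3% | 159 |
| 0.2 | 4% | 91.3% | 154 |
| 0.3 | 9% | 92.8% | 146 |

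The last column is rounded up, so it shows 161 where 160 was the input.

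**3. Chance imbalance.** With 200 randomized per arm, the shift that baseline imbalance induces in the unadjusted contrast has standard deviation r × 3.31 × √(2/200) = 0.331r kg. The 95% limits are 1.96 times that:

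- r = 0.1: 0.065 kg, 5% of 1.36 kg
- r = 0.2: 0.13 kg, 10%
- r = 0.3: 0.195 kg, 14%

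If the imbalance is taken among 160 analysed per arm instead, these limits grow by √(200/160) = 1.12, to about 0.22 kg at r = 0.3.

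**4. Is there bias?** In 4,000 simulated two-arm trials with 160 per arm and a true difference of −1.36 kg, the mean estimates were:

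- r = 0.2: −1.366 unadjusted and −1.366 adjusted; standard error 0.372 falling to 0.364
- r = 0.3: −1.359 unadjusted and −1.360 adjusted; standard error 0.369 falling to 0.354

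Both analyses are centred on the truth; only the spread differs.

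**5. Secondary continuous outcomes.** If the variance is equal at both visits and the baseline-to-follow-up correlation is ρ, the variance ratio of the adjusted analysis to the change score is (1 − ρ²)/[2(1 − ρ)] = (1 + ρ)/2. At an assumed ρ of 0.5 to 0.7 this is 0.75 to 0.85, a reduction of 15 to 25%. For noisier measures the gain can therefore exceed that for weight.

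**The case against.** The strongest reply is that the analysis is valid as it stands and the gain is small. That is right on validity: chance imbalance is already part of the unadjusted standard error. The gain may also be at the low end of the range. Subtracting baseline already removes most between-person variation in weight, entry BMI is confined to 21–30, and two weighings on a calibrated scale are averaged, which limits regression to the mean.

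A second reply is that a journal article condenses a fuller plan that may list more covariates, and that the text does not say site is the only one. This limits how firmly the point can be put. Still, the article does state a response and a covariate for its confirmatory model, and the comment addresses that stated method.

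Three stronger readings are tempting, and the documents support none of them.

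- A reader might infer that leaving out baseline weight biases the treatment contrast. Under randomization it does not, as step 4 shows.
- A reader might multiply a 10-point arm imbalance in the share with BMI ≥25 by the 5-lb gap between the Large Changes targets, reach 0.5 lb, and set it against the 3.0-lb design difference (17%). The target exists in one arm only. If the imbalance is split evenly, that arm departs from the pooled mix by 5 points, giving 0.05 × 5 = 0.25 lb. Even this assumes full attainment of the targets held throughout follow-up, whereas the article anticipates variable losses. With half the sample at BMI ≥25 (assumed), the standard error of the arm difference is √(2 × 0.25/200) = 5 points, so 10 points is a two-standard-error event. For Small Changes versus Control the mechanism is absent.
- A reader might take the BMI-dependent target as the reason to adjust. A target that acts in one arm is a treatment-by-BMI interaction, which a baseline main effect does not model and which the plan already tests.

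**Conclusion.** The point holds as a modest efficiency improvement to a valid primary analysis. The stated model leaves out a baseline measurement that is available on everyone and not balanced by design. For an assumed r of 0.1 to 0.3, adjusting for it cuts the variance by 1 to 9%, lifts power from 90% to about 90.3 to 92.8%, and removes a conditional shift with 95% limits of about 0.07 to 0.20 kg.

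These figures rest on the assumed r, on two-sided testing at 0.0167, and on an SD back-solved to give 90% power; the article supplies neither r nor the SD. If r is near zero the gain disappears, at negligible cost. Nothing here shows the stated power to be wrong or the planned comparison to be invalid.

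**What to change.** State in the Analysis plan that the primary longitudinal model includes baseline weight and its interaction with visit alongside clinic site, and that the 24-month contrast comes from that same model. State that each continuous behaviour and risk-factor model includes that outcome's own baseline value.

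Leave the yes/no weight-gain GEE unchanged. Its link is not stated. Under a logit link, adding a baseline covariate would turn a marginal odds ratio into a conditional one, while the Sample size calculation section powers that outcome on a relative reduction in a proportion. Leave the prespecified BMI interaction test as the place to examine the BMI-dependent target.

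The cost is a sentence or two of analysis wording and a few model terms, with no new data. It should be fixed before outcomes are seen by arm, because a covariate added after an imbalance is noticed is open to challenge.

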### Active interventions: common components

The two active interventions tested in SNAP are both based on self-regulation theory and share an emphasis on daily self-weighing; they also have the same frequency of interventionist contact (see Table 2), provide the same basic information about healthy eating and physical activity, and teach participants identical behavior modification skills to facilitate the prescribed behavior changes (small or large). The same interventionists, who have master’s level backgrounds in nutrition, exercise physiology or psychology, and previous behavioral weight control experience, lead groups for both intervention arms.

**Table 2 T2:** Schedule of intervention contact

**Time frame**	**Meetings**	**Reporting weight**
Year 1		
Months 1-2	Weekly face-to-face (8 total)	None*
Months 3-4	Monthly face-to-face (2 total)	Weekly
Months 5-12	None	Monthly
Year 2	Two annual 4 week refreshers: offered in different formats (face-to-face; online; email)	Monthly
Year 3	Two annual 4 week refreshers: offered in different formats (face-to-face; online; email)	Monthly

*No reporting is needed since participants are weighed at weekly meetings.

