#### Intervention contact

The core content of both intervention conditions is delivered in 8 weekly group sessions, followed by 2 monthly groups (e.g., initial 10 session program delivered over 16 weeks). Following initial treatment, monthly contact from the SNAP team is maintained primarily via automated reminder emails for weight submission, and a monthly email with feedback on weight zone and recommended behavioral strategies. Additional modalities are used depending on participant zone status, including monthly postal mail for sending token reinforcers, and phone, email or in-person contact if requested by participants who have gained above baseline. Two annual refresher campaigns (4 weeks in duration) are offered using in-person sessions, email or other Internet modalities to offer different approaches to appeal to different participants. While refresher formats may vary over time, the identical format (with content/goals appropriate for the treatment condition) is offered to Small and Large Changes.

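### Both active arms are delivered in groups, but the stated primary model treats members of a group as independent; if outcomes correlate within groups, the promised error control is lost

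*Protocol article*

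**What the plan says.** Delivery (protocol article, Intervention contact and Table 2): "The core content of both intervention conditions is delivered in 8 weekly group sessions, followed by 2 monthly groups". Refresher courses in later years may also be face-to-face. Under Active interventions: common components, the same interventionists "lead groups for both intervention arms". The Self-guided behavior changes section gives control participants a single group session. Participants are randomized individually.

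Analysis (Analysis plan): weight changes are contrasted "using generalized linear models fitted by maximum likelihood with an unstructured covariance matrix", with clinic site as a covariate. Pairwise differences are tested with Wald statistics, "using Bonferroni adjustment to control total Type I error to be 0.05 across the three comparisons". The yes/no weight-gain outcome is analysed by GEE.

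Sample size (Sample size calculation): 200 per arm "is projected to provide ≥ 90% statistical power to detect an average pairwise difference of 3.0 lbs (1.36 kg) weight change over time", allowing for stated rates of loss to follow-up. No standard deviation, ICC, group size or design effect is given there or elsewhere in the article.

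**The concern.** People who share ten sessions share a leader, a group climate and each other's ideas. In Small Changes the participants devise possible dietary changes together as part of the lesson. Their weight outcomes may therefore be correlated. Control participants meet once, so any such correlation sits mainly in two of the three arms: a partially nested design.

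The stated model has no place for it. In a repeated-measures model the unstructured matrix describes how one participant's weights at different visits relate to each other. It does not link different participants. There are two sites, so a site covariate removes a difference between Providence and North Carolina but not differences between session groups within either.

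This goes beyond a detail left to a fuller document. The article fixes the estimator, covariance structure, covariate, test and multiplicity rule, and that combination assumes independence between members of a session group. At stake is the error rate the plan undertakes to hold, above all for Small versus Large Changes, where both arms are affected and which the article describes as never before compared in a trial.

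**Working it through.** **Inputs from the article.** 200 per arm; power of at least 90%; difference 1.36 kg; total Type I error 0.05 over three comparisons, so 0.05/3 = 0.0167 each. Two-sided testing is stated for the 24-month secondary aim and assumed here for the primary tests, giving a critical value of 2.394.

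**Assumed, because the article does not give them.** Session-group size m = 10 to 20; ICC = 0.01 to 0.05.

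**Step 1: the plan's own power figure.** It cannot be reproduced, because no standard deviation is given and the paragraph does not say which alpha it used. Working backwards, exactly 90% at 0.0167 needs a standard error of 1.36/(2.394 + 1.282) = 1.36/3.676 = 0.370 kg. With 200 per arm the standard error is SD × √(2/200) = 0.1 × SD, so SD = 3.70 kg (4.20 kg at an unadjusted 0.05). With 150 per arm the values are 3.20 kg and 3.63 kg. The article has nothing to compare these with.

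**Step 2: variance inflation.** Design effect DE = 1 + (m − 1) × ICC. For Small versus Large both arms are inflated, so the variance factor is VF = DE. For active versus control only one arm is, so VF = (1 + DE)/2.

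**Step 3: actual per-test level of the stated model.** Level = 2 × [1 − Φ(2.394/√VF)]. For m = 15 and ICC = 0.02: DE = 1 + 14 × 0.02 = 1.28; √1.28 = 1.131; 2.394/1.131 = 2.116; level = 0.034.

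**Step 4: power of a test that does hold 0.0167, if the starting power is exactly 90%.** Power = Φ(3.676/√VF − 2.394). For the same case: 3.676/1.131 − 2.394 = 0.855, giving 0.804.

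| m, ICC | DE | Small vs Large: true SE ÷ model SE | level | power | Active vs control: true SE ÷ model SE | level | power |
|---|---|---|---|---|---|---|---|
| any, 0 | 1.00 | 1.00 | 0.0167 | 0.900 | 1.00 | 0.0167 | 0.900 |
| 10, 0.01 | 1.09 | 1.04 | 0.022 | 0.870 | 1.02 | 0.019 | 0.885 |
| 15, 0.02 | 1.28 | 1.13 | 0.034 | 0.804 | 1.07 | 0.025 | 0.853 |
| 20, 0.05 | 1.95 | 1.40 | 0.087 | 0.594 | 1.21 | 0.049 | 0.736 |

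**Step 5: the total of 0.05.** Bonferroni guarantees it because three levels of 0.0167 sum to 0.05. In the three clustered rows the sums (one Small-versus-Large test plus two active-versus-control tests) are 0.022 + 2 × 0.019 = 0.060, 0.034 + 2 × 0.025 = 0.084, and 0.087 + 2 × 0.049 = 0.185. These are ceilings on the familywise error, not the error itself. Bonferroni is somewhat conservative for three overlapping contrasts, so a very small ICC could be absorbed. In the last row the Small-versus-Large test alone exceeds 0.05.

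**Step 6: margin in the power.** The article states a floor. If the starting power were 95%, power of 90% would survive DE up to [(2.394 + 1.645)/3.676]² = 1.21 with both arms clustered. If it were 99%, it would survive DE up to [(2.394 + 2.326)/3.676]² = 1.65.

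**Step 7: dropout.** Planned loss adds to 7.5 + 7.5 + 5 + 5 = 25% by month 36, so a group of 20 shrinks to 15. At ICC 0.05, DE is then 1 + 14 × 0.05 = 1.70 rather than 1.95. For Small versus Large the level is 0.066 rather than 0.087, and power 0.665 rather than 0.594.

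**The case against.** The strongest reply is that every figure above rests on an ICC and a group size that the article does not give, and that the assumed range runs from trivial to serious. This stands. At ICC zero nothing changes. A reader might infer that the standard errors are too small as a matter of fact; the article does not support that. It supports only the conditional statement.

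A reader might also infer that true power is below 90%. That is not supported either. The statement is a floor, no standard deviation is given, and Step 6 shows that a comfortable margin could absorb moderate clustering. A condensed article may also leave a clustering allowance to the full protocol.

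Other points also reduce the likely size:

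- Group sessions are concentrated in the first four months. Later contact is mainly by email, web or text message, with individual sessions for those above baseline weight. Correlation by initial group may fade over 24 to 48 months, although the month-4 weight, taken as the group programme ends, enters the primary outcome.
- Fixed group membership is not stated. The sequenced eight-week curriculum suggests it, but make-up sessions and materials sent to absentees loosen it.
- The number of interventionists is not given. They lead groups in both active arms, so leader effects common to both tend to cancel in Small versus Large. Effects specific to a session group do not cancel, which is why the session group is the unit to model.

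None of this gives the stated model a way to detect or allow for the correlation. A fuller analysis plan may contain a group term; if so, pointing to it settles the analysis part.

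**Conclusion.** The point holds as a conditional one, with moderate confidence. The model as stated assumes independence between members of a session group, and neither the unstructured covariance nor the site covariate relaxes that. If the within-group ICC is above zero, standard errors are understated and the Bonferroni guarantee lapses, with about twice the extra variance for Small versus Large as for either comparison with control. Under the assumed ranges, the inflation runs from slight to about five times the nominal level (0.087/0.0167 = 5.2), with the top end unlikely for the reasons above.

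On power, the supportable statement is narrower: loss to follow-up is the only allowance the paragraph names, so the reader cannot tell whether at least 90% survives clustering. The GEE analysis of weight gain has the same gap, and there the article states 90% without presenting it as a floor.

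This is a worthwhile and cheap improvement to the stated model. It is not a defect that must be cured before the trial can be interpreted.

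**What to change.** In the primary model, add a random effect for the initially assigned session group in the two active arms only, treating control participants as unclustered (a partially nested model). Alternatively, use cluster-robust variance on that unit. In either case, base small-sample degrees of freedom on the number of session groups. Define the unit by initial assignment, not by sessions attended, so that make-up sessions do not change it. Apply the same structure to the GEE for weight gain. In the sample size section, show power over a stated range of ICC and group size, together with the standard deviation and alpha used.

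The cost is a few sentences and one group identifier, which must be kept in the analysis file. Intervals will be somewhat wider if the ICC is positive, and the stated power may be lower. If the ICC proves negligible, little is lost.

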## Methods

### Study design

SNAP targets the enrollment of 600 participants, who are randomly assigned with equal probability to 1 of 3 treatment groups, stratified by clinical center:

1. Self-guided behavior changes (Control)

2. Self-Regulation Plus Small Behavior Changes

3. Self-Regulation Plus Large Behavior Changes

Assessments are completed at baseline, 4, 12, 24, 36 and 48 months. Since enrollment is staggered, all participants are scheduled to complete the 24-month follow-up, 80% are scheduled to complete 36 months and 20% are scheduled to complete the 48-month assessments. The study was approved by the Institutional Review Boards at Lifespan-The Miriam Hospital, The University of North Carolina at Chapel Hill and Wake Forest University Health Sciences.

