### Randomization

Randomization follows a simple, non-adaptive variable-block length algorithm, which is stratified by clinical site and by gender and ethnicity (Non-Hispanic white versus other race/ethnic groups).

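### The primary model names clinic site as its covariate but not gender and ethnicity, which are also randomisation strata; the cost is a small, avoidable loss of precision

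*Protocol article*

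**What the plan says.** Three sections of the protocol article bear on this.

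- **Randomization** describes a variable-block scheme "stratified by clinical site and by gender and ethnicity (Non-Hispanic white versus other race/ethnic groups"). With two sites and two levels each for gender and ethnicity, this makes 2 × 2 × 2 = 8 strata.
- **Study design** describes participants "who are randomly assigned with equal probability to 1 of 3 treatment groups, stratified by clinical center". It mentions no other factor.
- **Analysis plan** specifies the primary comparison as "generalized linear models fitted by maximum likelihood with an unstructured covariance matrix", "with clinic site included as a covariate". Pairwise contrasts are tested with Wald statistics, "using Bonferroni adjustment to control total Type I error to be 0.05 across the three comparisons".

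The article itself treats the two omitted factors as possibly relevant to weight change. Study aims lists ethnicity among the variables that may predict weight change or moderate the interventions, and the Analysis plan makes gender a pre-specified subgroup.

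**The concern.** Blocked randomisation within strata balances gender and ethnicity across the arms. Where those factors are prognostic, the balance makes the treatment contrast less variable than under unstratified allocation. A model without them does not recognise this: their variation stays in the residual, and the model-based standard error describes a noisier experiment than the one conducted. The Wald tests are then conservative, and some of the precision bought by stratification is not used.

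This differs from a covariate list left to the analysis plan. The article fixes the estimation method, covariance structure, covariate, contrasts, test and multiplicity rule, and the one covariate it names is one of the three strata.

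Gender has a second relevance. Weights during pregnancy and for six months post-partum are excluded, and the retention section calls pregnancy the biggest source of dropout in earlier studies of this age group. Missing weights will therefore depend partly on gender, and the primary analysis assumes they are missing at random. Having gender in the model makes that assumption easier to defend.

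**Working it through.** **Inputs**

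- Total Type I error 0.05 over three comparisons (Analysis plan), so 0.05/3 = 0.0167 each.
- Two-sided testing. The Analysis plan says "Two-sided tests will be used with Bonferroni-adjustment" for the 24-month aim; I assume the same for the primary. The critical value is then 2.394.
- 200 per arm, a 1.36 kg difference and at least 90% power (Sample size calculation).
- Loss of 7.5% + 7.5% + 5% + 5% = 25% by month 36 (same section), leaving 200 × 0.75 = 150 per arm.
- R², the share of weight-change variance explained by gender and ethnicity: **not given**. I assume 0% to 10%.

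**The plan's own figure.** The 90% cannot be reproduced because no SD is stated. Solving for the largest SD that gives 90% power with 150 per arm:

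SD = 1.36 × √(150/2) / (2.394 + 1.282) = 3.20 kg.

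The standardised effect is then 2.394 + 1.282 = 3.676. I take this as the starting point, so that R² = 0 gives 90.0% for both analyses.

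**Formulas**

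1. Overstatement of the reported standard error in the site-only model: 1/√(1 − R²).
2. Power of the site-only model under stratified blocks. The estimate's true standard error has shrunk by √(1 − R²) while the reported one has not: Φ((3.676 − 2.394)/√(1 − R²)).
3. Power with all strata in the model: Φ(3.676/√(1 − R²) − 2.394).

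| Assumed R² | Reported SE too large by | Power, site only | Power, all strata | Gain (points) |
|---|---|---|---|---|
| 0% | 0.0% | 90.0% | 90.0% | 0.0 |
| 2% | 1.0% | 90.2% | 90.6% | 0.4 |
| 5% | 2.6% | 90.6% | 91.6% | 1.0 |
| 10% | 5.4% | 91.2% | 93.1% | 1.9 |

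**Simulation check.** Permuted blocks in 8 strata, 25% men and 25% minority (the recruitment floors in Eligibility), 25% random loss, a single change score, and 2,000 runs for each R².

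| R² | Mean reported SE, site only | Mean reported SE, all strata | Power, site only | Power, all strata |
|---|---|---|---|---|
| 2% | 0.370 | 0.366 | 89.5% | 90.3% |
| 5% | 0.370 | 0.360 | 90.0% | 91.1% |
| 10% | 0.370 | 0.351 | 91.1% | 93.2% |

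The site-only standard error does not fall as R² rises, while the adjusted one does, as the formulas say. The power differences of roughly 1 to 2 points agree with the formulas within simulation error. Rejection rates under no effect were 0.0155 to 0.0205 (site only) and 0.016 to 0.0225 (all strata). The Monte Carlo standard error at 0.0167 is √(0.0167 × 0.9833/2000) = 0.0029, so these are close to nominal, and the runs are too few to show the slight conservatism.

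**How plausible is the upper end?** With the same 25%/25% split, independent factors, equal shares of R² and SD 3.20 kg, each factor must shift mean weight change by 3.20 × √(R²/2)/√(0.25 × 0.75). This is 1.17 kg at R² = 5% and about 1.65 kg at R² = 10%. The latter exceeds the 1.36 kg treatment difference the trial is powered to detect.

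**The case against.** Four objections deserve weight.

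**The two design sections need not conflict.** A reader might infer that Study design restricts stratification to center. It does not: the words are "stratified by clinical center", without any "only", in an overview sentence, and Randomization is the dedicated section. Both can be true. This stands: it is an incomplete summary to be aligned, not a proven contradiction.

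**The covariate wording is not exclusive, and a fuller list may exist elsewhere.** This is partly right. The article does not call site the sole covariate. But it sets out the primary model in detail and names one stratum of three, so the mismatch is in the stated text.

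**The benefit is easy to overstate.** One might hold site-only power at 90.0% and read the gain as 1.6 or 3.1 points at R² of 5% or 10%, or as 12 to 60 participants saved (3 arms × 200 × R², for R² of 2% to 10%). That compares the adjusted analysis with a trial whose sampling error had not been reduced by stratification. Site-only power also rises under stratified blocks, so the gain is about 1.0 or 1.9 points. R² is also wholly assumed, and the outcome is change in weight, so differences in absolute weight between men and women do not count. This objection stands in full.

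**Adjustment is not free in every model.** A reader might extend the fix to the GEE for gaining more than one pound. The article names no covariates there, so there is no stated mismatch. The link is not stated either; under a logit link, added covariates can change the odds ratio being estimated. This stands, and the GEE is left out.

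Nor do the documents support reading the omission as a threat to validity. Its effect is conservative, and it does not undermine the stated power of at least 90%.

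**Conclusion.** The point holds as a modest matter of efficiency and consistency. The primary model's named covariate does not match the full set of randomisation strata. If gender and ethnicity predict weight change, the reported standard errors will be somewhat too large and the three pairwise tests slightly conservative.

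The size rests entirely on the assumed R². It also takes a back-solved SD of 3.20 kg, 150 per arm at month 36, two-sided testing at 0.0167, and balance across arms that survives dropout. Within that frame the gain runs from nothing to just under 2 percentage points of power, and is under half a point if R² is 2% or less. I am confident of the direction; the documents cannot settle the size. The link between gender and pregnancy-related missingness is a further reason to adjust, but I have not quantified it.

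**What to change.** 1. In Study design, name the same stratification factors as in Randomization, after confirming which were implemented.
2. In the Analysis plan, state that the primary linear model includes every factor actually used in randomisation as fixed effects. If Randomization is right, these are clinic site, gender and race/ethnicity (non-Hispanic white versus other). The 24-month contrast, which is drawn from the same model framework, should use the same terms.
3. Leave the GEE for the binary outcome outside this change.

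The cost is two short wording changes. No new data are needed, because the factors must be known at randomisation. The change should be made before unblinded outcome data are analysed, so that the covariate set cannot look chosen after the fact.

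A suitable sentence would be: *The primary model will include fixed effects for all factors used to stratify randomisation (clinic site, gender, and race/ethnicity as non-Hispanic white versus other).*
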